## Abstract

**Background:**

Enteric fever is estimated to affect 11–20 million people worldwide each year. Morbidity and mortality from enteric fever primarily occur in lower-income countries, with children under 5 years of age experiencing a significant portion of the burden. Over the last few decades, the control of enteric fever has focused primarily on improved water and sanitation, with the available vaccines unsuitable for children and primarily used by travelers. A new typhoid conjugate vaccine (Vi-TCV), prequalified by the World Health Organization (WHO) and highly immunogenic in children under 5, has the potential to reduce the typhoid burden in endemic countries.

**Methods:**

This study is a double-blinded, randomized, controlled trial with a 2-year follow-up to assess the protective impact of the Vi-TCV vaccine, compared with a control vaccine, in children from 9 months to 16 years of age. The primary outcome of interest is the reduction in the number of culture-confirmed typhoid cases attributable to Vi-TCV. Approximately 20 000 children living in the Lalitpur district, within the Kathmandu valley, will be enrolled in the study and followed to measure both safety and efficacy data, which will include adverse events, hospitalizations, antibiotic use, and fever frequency.

**Results:**

Both the intervention and control vaccines are WHO prequalified vaccines, which provide a health benefit to all participants. Children have been chosen to participate because they bear a substantial burden of both typhoid morbidity and mortality in this population. The results of this study will be disseminated through a series of published articles. The findings will also be made available to the participants and the broader community, as well as local stakeholders, within Nepal.

**Conclusions:**

This is the first large-scale, individually randomized, controlled trial of Vi-TCV in children in an endemic setting, and will provide new data on Vi-TCV field efficacy. With Vi-TCV introduction being considered in high-burden countries, this study will support important policy decisions.

**Clinical Trials Registration:**

The trial is registered on the ISRCTN registry (for details, see https://doi.org/10.1186/ISRCTN43385161; registry number: ISRCTN 43385161).

Enteric fever, including typhoid fever, is a systemic illness caused by the human restricted pathogens *Salmonella enterica* serovars Typhi and Paratyphi. It is estimated to affect 11–20 million people worldwide annually, with an estimated 100 000 to 200 000 fatalities per annum, primarily in lower-income countries with poor quality water and inadequate sanitation [1, 2]. Areas with an incidence of >100/100 000 are considered endemic, including many countries in Africa, South Asia, South-East Asia, and Central Asia [3]. The burden of disease and mortality is increasingly recognized in the under 5 age group, as well as in older children and young adults [4–8]. Enteric fever also remains a concern in high-income countries, for travelers to endemic regions and laboratory workers [9, 10].

Control of typhoid fever, historically, has been achieved primarily through improved water and sanitation infrastructure, leading to the elimination of disease as a public health problem from most developed countries. While improved sanitation is the most effective solution to preventing widespread typhoid, there are substantial costs and difficulties in implementing these measures rapidly in resource-poor settings. As such, the use of an effective vaccination program targeting the highest-risk populations will likely be a useful and cost-effective addition to control measures [8]. Given the causative organisms are human-restricted, global eradication is possible and an effective vaccine can support elimination efforts.

Previous efforts to control typhoid through vaccination have had limited success [2, 11]. 3 typhoid vaccines have previously been licensed: the inactivated whole-cell vaccine, the polysaccharide vaccine (Vi-PS), and Ty21a [11]. Vi-PS and Ty21a are currently available, but have failed to be used routinely in endemic typhoid countries, due to either age restrictions and/or a lack of feasibility (multiple doses) [2, 6, 11–16]. A prior typhoid conjugate vaccine (TCV) (Vi-rEPA), was highly efficacious in a clinical trial in Vietnam and was shown to be immunogenic in infants, but was never commercialized [17, 18].

Vi-TCV (Tybar-TCV) is a newly available vaccine developed by Bharat Biotech and consisting of 25 µg of Vi polysaccharide antigen conjugated to a tetanus toxoid carrier protein. Vi-TCV induces a T-cell–dependent response. It can, therefore, induce antibody responses in infants and young children under 2 years of age and has the potential to generate durable immune responses via the induction of immunological memory.

A Phase III, randomized, controlled trial comparing Vi-TCV with Vi-PS in sub-groups receiving boosters of either vaccine at 2 years demonstrated significantly higher anti-Vi immunoglobin G (IgG) titres in the Vi-TCV group compared with the Vi-PS group in participants aged 2 years to 45 years (titres of 1685.3 EU/ml [95% confidence interval {CI} 1468–1797] in Vi-TCV vs 445.6 EU/ml [95% CI 323–615] in Vi-PS) [19]. An open-label trial conducted alongside this assessed the immunogenicity of a single dose of Vi-TCV in infants and toddlers aged 6–23 months and demonstrated seroconversion to anti-Vi IgG [19]. Safety data from the same study demonstrated that Vi-TCV was well tolerated by all age groups [20].

Efficacy data are available from a recent controlled human infection study at the University of Oxford [21]. The study measured the efficacy of single doses of Vi-TCV, Vi-PS, and a control vaccine against typhoid infection after an oral challenge. The study was conducted in healthy, United Kingdom adult volunteers and the challenge was performed 28 days after vaccination. Using a composite diagnostic endpoint of clinical and/or microbiologically-confirmed typhoid fever, the Vi-TCV and Vi-PS vaccines demonstrated comparable protective efficacies of 54.6% (95% CI 26.8–71.8%) and 52.0% (95% CI 23.2–70.0%), respectively, when compared with the control vaccine [21]. When applying a definition of typhoid fever which more closely approximates diagnoses in health-care settings—that is, fever, followed by confirmatory bacteraemia—in a post hoc analysis, the protective efficacy of the Vi-TCV vaccine was 87.1% (95% CI 44.2–96.9%), compared with 52.3% (95% CI -4.2 to 78.2%) for the Vi-PS vaccine[21].

The data from seroconversion and efficacy studies are strong, with 1 study showing a seroefficacy of 85% (95% CI 80–88%) [22]. Large-scale field impact studies for Vi-TCV, demonstrating a reduction in the burden of disease attributable to typhoid infections, have not yet been conducted, and this vaccine is currently not used routinely in Nepal.

Vi-TCV is licensed for use in India and Nepal, and has been WHO prequalified for broad use [23]. Despite this, TCV is still not available for use in Nepal through routine vaccination or at private clinics. This study will assess the impact of Vi-TCV in a field setting in order to inform and support the use of the vaccine as a control measure for typhoid fever in endemic settings, and to reduce global morbidity and mortality from typhoid fever. Vi-TCV has shown promise from existing studies; it can produce seroconversion in infants; it potentially produces long-lasting immunity; and it is efficacious in a controlled challenge setting. As such, it is an obvious candidate to test in a field impact study. The primary objective of this trial is to determine how effective Vi-TCV is at preventing blood culture–confirmed symptomatic infections caused by *S.* Typhi.

Our secondary objectives are to investigate the safety outcomes associated with Vi-TCV; determine the impact of vaccination with Vi-TCV on the incidence of admission rates for fever; measure the number of days spent in hospitals from febrile illnesses; measure the differences in rates of hospital/clinic presentations for febrile illnesses; measure paratyphoid infection rates; and measure the incidence of clinically-suspected enteric fever. Some of the exploratory objectives are to measure self-reported and/or prescribed antibiotic/antimicrobial use for inpatients/outpatients; determine the effect of vaccination on growth and weight in children <5 years of age; determine the immunogenicity of Vi-TCV and the persistence of antibodies induced by Vi-TCV; and measure all-cause mortality and all-cause mortality with fever.

## METHODS AND ANALYSIS

### Study Design

This is a participant- and observer-blind, individually randomized, controlled trial with a 2-year follow-up to assess the protective impact of Vi-TCV.

### Population

Children aged 9 months to <16 years at the time of enrollment will be eligible to participate. Participants will be identified as living within the defined catchment area of the Lalitpur district, within the Kathmandu valley, Nepal. Trial staff, including local community health volunteers, will identify households with children <16 years of age and approach them for participation.

This age range has been selected because children bear a substantial burden of the disease in both mortality and morbidity, without an effective vaccine available in the routine vaccination schedule. Therefore, this demographic group has the most to gain from vaccination with Vi-TCV and would be the primary target for any subsequent vaccination campaign.

#### Inclusion Criteria

To be included in the study, the following inclusion criteria must be met:

Parent/legal guardian is willing and competent to provide informed consent. If the participant is 7 years of age or older, assent will also be sought.Participant is aged between 9 months and <16 years (ie, up to 15 years and 364 days) at the time of vaccination.Participant is in good health on the day of vaccination.Parent/legal guardian confirms that they/their child will be willing and able to comply with the study requirements, including follow-up contacts, according the schedule (Table 1).Participant lives within the study catchment area at the time of vaccination.

#### Exclusion Criteria

Any of the following criteria will be grounds for exclusion:

Participant has knowingly received a typhoid vaccine in the last 3 years.Participant has a known allergy to any of the vaccine components.Participant or parent/guardian has any medical or social reason that will prevent the participant from conforming to the study requirements, as judged by a medical professional.Participant or parent/guardian is planning to move away from the catchment area within the next 6 months.

### Study Setting

The study setting of the Lalitpur district, within the Kathmandu valley, Nepal, has been chosen because enteric fever is endemic to Nepal, with a high incidence in Kathmandu. The Strategic Typhoid Alliance Across Africa and Asia has conducted passive surveillance of typhoid and paratyphoid incidences in the study area of Kathmandu, providing baseline typhoid rates for comparison [24].

Typhoid has been recognized locally as a public health concern, and there is political support and interest for the introduction of a new typhoid vaccine for children.

### Intervention and Randomization

Vi-TCV will be the intervention vaccine, and a Meningococcal serogroup A vaccine (MenAfriVac) against *Neisseria meningitidis* serogroup A (MenA), manufactured by the Serum Institute of India, will be the control vaccine.

Participants will be randomized in a 1:1 ratio to receive either the Vi-TCV or MenA vaccine, using stratified block randomization with randomly varying block sizes from 6–12. Stratification will be by age (9 months to <5 years old or ≥5 years old to <16 years). Participant randomization will occur at the vaccination visit, using a purpose-built, offline, mobile application. Individual logins will be given to unblinded staff, which will allow secure access to the application. No trial staff will be able to make changes to randomization information stored on the application.

In addition, for those who consent to blood collection, the same mobile application will be used to randomly select 1500 individuals to be included in an immunogenicity sub-study. Blood sampling randomization will be on a 2:1 basis (1000 Vi-TCV and 500 MenA) and be age stratified (<5 years and ≥5 years). A diagram of planned trial activities can be seen in Figure 1.

**Figure 1. F1:**
[figure not shown]
Flow chart of planned trial participant contact. Abbreviation: TCV, typhoid conjugate vaccine.

In order to maintain blinding, randomization and vaccine preparation will take place behind a curtain, where only unblinded staff are permitted. Follow-up contacts will not be undertaken by unblinded staff ([name] & [name] et al, *in progress in this supplement*). Unblinding will take place after the 2-year follow-up period has been completed.

Portable servers, accessible through an Intranet, will be set up in each clinic and data will be directly entered onto laptops connected to a local server [[name] and [name], *in progress in this supplement*]. The local server will be transported to a facility with an Internet connection daily, and the data collected during that day will be uploaded onto the main server.

### Passive Surveillance and Participant Follow-up

Passive surveillance will be conducted at the local hospital and in community-based health clinics. Trial participants who present with ≥2 days of subjective, persistent fever or a temperature of at least 38 degrees C at presentation will be tested for typhoid via blood culture. Enteric fever cases will be treated with antibiotics and followed for resolution (Figure 2). Hospitalization, surgical procedures for perforation, and other serious outcomes will be followed and recorded. Participants will be contacted every 3 months to follow up on recent fevers, antibiotic use, and other health outcomes of interest (Table 1). Medical record reviews will be performed if a participant follow-up contact identifies a fever and/or hospitalization.

**Table 1. T1:** Visit and Sample Schedule

Visit	1	2	3	4	5	6	7	8	9	10	11^a^
Day	0	7	28	90	180	270	365	455	545	635	730
Permissible time window (days)	…	+7/-1	±4	±14	±28	±28	±56	±56	±56	±56	±90
Screening	X	…	…	…	…	…	…	…	…	…	…
Consent	X	…	…	…	…	…	…	…	…	…	…
Randomization	X	…	…	…	…	…	…	…	…	…	…
Vaccination	X	…	…	…	…	…	…	…	…	…	…
Medical history and exam	X	…	…	…	…	…	…	…	…	…	…
Blood collection^b^	X	…	X	…	…	…	…	…	X	…	X
Height and weight^c^	X	…	…	…	…	…	…	…	…	…	X
Follow-up contact^d^	…	X^e^		X	X	X	X	X	X	X	X
Vaccination with either Vi-TCV or MenA^f^	…	…	…	…	…	…	…	…	…	…	X
Documentation of vaccine receipt^g^	X	…	…	…	…	…	…	…	…	…	X

Abbreviations: AEFI, adverse event following immunisation; MenA, *Neisseria meningitidis* serogroup A; TCV, typhoid conjugate vaccine.

^a^Ideally, all of the visit 11 activities will occur simultaneously, but the follow-up contact may occur separately, if necessary.

^b^Blood sampling for immunogenicity will be in a subset of 1000 Vi-TCV and 500 control participants. The planned blood draws are ~5 ml per visit. The total maximum volume will be ~20 ml per participant. The blood draw on Day 0 will occur before vaccination; the blood draw at Day 545 will aim to occur at the same time as the follow-up; and the blood draw at Day 730 will occur at the same time as unblinding and vaccine documentation.

^c^Height and weight will be measured only in children under 5 years of age at the time of enrollment.

^d^Follow-up contact includes: ensuring the participant and family still live in the area and are happy to continue with the study; inquiring regarding work and school absenteeism; recording mortality and morbidity in the participant, including fevers; and providing a reminder to attend a trial health-care facility if they develop a fever of ≥2 days.

^e^At 7 days, full AEFI reporting will be collected during the follow-up contact.

^f^Either Vi-TCV or MenA vaccine will offered at the end of the trial, depending on which vaccine the child initially received.

^g^Both the intervention and control arms will be asked to return for unblinding (at Day 730 only) and documentation of vaccination.

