**Figure 2. F2:**
[figure not shown]
Unscheduled procedures flow chart.

The proportion of participants developing adverse events within 7 days of vaccination and serious adverse events within 6 months of vaccination will be identified through both active follow-up contacts (telephone and in person) and self-reporting by participants.

An immunogenicity sub-study will investigate the immune response to the vaccine by drawing blood 4 times throughout the study: on Day 0, on Day 28, at 18 months, and at 2 years post-vaccination. These blood samples will also be used to investigate the duration and persistence of IgG Vi-antibodies, using enzyme-linked immunosorbent assay (ELISA) vacyme, over time.

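### The Visit 2 window lets the only scheduled full AEFI contact take place on Day 6, before the 7-day adverse-event period is complete (low severity)

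*Protocol article*

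**What the plan says.** Four statements in the protocol article bear on this point.

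- **Schedule.** Table 1 counts days from vaccination on Day 0 ("Day 0 7 28 90 180") and gives Visit 2, at Day 7, the window "Permissible time window (days) … +7/-1".
- **Collection.** Footnote e to Table 1: "At 7 days, full AEFI reporting will be collected during the follow-up contact". No other visit carries this footnote.
- **Outcome.** The section Passive Surveillance and Participant Follow-up, after Figure 2, defines the measure as "The proportion of participants developing adverse events within 7 days of vaccination". It says that events "will be identified through both active follow-up contacts (telephone and in person) and self-reporting by participants".
- **Later contacts.** Footnote d says that follow-up contacts include "recording mortality and morbidity in the participant, including fevers". In Table 1 the follow-up row has no mark at Visit 3 (Day 28). The next marked contact is Visit 4, at Day 90 ±14.

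Safety is a secondary objective, listed first in the introduction: "Our secondary objectives are to investigate the safety outcomes associated with Vi-TCV".

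**The concern.** The outcome period, the collection point and the window are all printed in the article, and they do not fit together. A contact on Day 6 complies with the schedule but comes before 7 days have passed. An event that starts after that contact and still inside the period has no second full AEFI enquiry to catch it.

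Any error goes one way: an early contact can miss events but cannot add them. What is at stake is the absolute proportion of children with an adverse event in the first week. Unless early contacts are flagged, a no-event answer on Day 6 looks the same as one given after the whole period.

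**Working it through.** The article gives no adverse-event rate, safety sample size or safety power, so there is no stated figure to reproduce. The check is arithmetic on the windows, followed by an illustration on assumed inputs.

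**1. Windows (Table 1)**
- Visit 2: 7 − 1 = Day 6 to 7 + 7 = Day 14, which is 9 permitted days. One lies before Day 7; eight lie on or after it.
- Next follow-up contact: 90 − 14 = Day 76 to 90 + 14 = Day 104.
- Visit 3 is marked only for blood collection, in the immunogenicity subset of 1500.

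**2. Length of the gap after a Day 6 contact**

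The article does not say how the 7 days are counted.
- Days 0 to 6 (seven calendar days): the contact falls on the last day, and at most the rest of that day is missed.
- Through Day 7: about one day is missed.

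**3. Size of the loss**

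Relative loss in the 7-day proportion = f × g × (1 − s), where
- f = share of children contacted on Day 6;
- g = among children with a 7-day event, the share whose only event starts after a Day 6 contact;
- s = share of those events recovered by self-report or at a later contact.

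The article gives none of these, so all are assumptions. For uniform onset, g = 1/8 (Days 0 to 7) or 1/7 (Days 1 to 7).

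| Assumed case | f | g | s | Relative loss |
|---|---|---|---|---|
| Contacts and onsets uniform | 1/9 | 1/8 to 1/7 | 0 | 1.4% to 1.6% |
| Contacts uniform, few late onsets | 1/9 | 5% | 0 | 0.6% |
| Contacts uniform, very few late onsets | 1/9 | 1% | 0 | 0.1% |
| Every contact on Day 6, onsets uniform | 1 | 1/8 to 1/7 | 0 | 12.5% to 14.3% |

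For example, 1/9 × 1/7 = 0.0159. With s = 0.5 every entry halves.

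Under uniform contact timing, about 20 000 / 9 ≈ 2 200 children would be contacted on Day 6. That is the number contacted early, not the number of missed events.

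**4. After the change**

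With +7/-0 the window is Day 7 to Day 14, so f = 0 and the loss from Day 6 contacts is 0.

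**The case against.** The strongest reply is that little follows from one permitted early day. Eight of the nine permitted days are unaffected. Visit 2 is not the only source of adverse-event data: self-reports also feed the outcome, and later contacts record morbidity. If the period is Days 0 to 6, almost nothing is lost. The day count and the handling of partial follow-up may well be set out in the full protocol or the SAP, which are not shown.

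Most of this stands, and it limits the size of the point. It does not remove the mismatch. Unprompted reporting is not equivalent to a full AEFI enquiry, and the next scheduled contact is about ten weeks later and not marked for one. Even under the shorter count, the contact can precede the end of the period.

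A reader might infer that the 7-day proportion is under-ascertained by design, or that every child contacted on Day 6 is counted as fully followed. The article supports neither. Only Day 6 contacts are exposed, and only where the sole event starts later and is not otherwise reported. The article does not say how such children enter the analysis.

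A reader might also suspect a biased comparison of the arms. Both arms share the window, and "Follow-up contacts will not be undertaken by unblinded staff", so nothing in the article points that way. An equal relative loss in both arms would leave their ratio unchanged.

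**Conclusion.** The point holds as a minor misalignment. The window allows the only scheduled full AEFI contact to precede the end of the period it is meant to cover. For children contacted on Day 6, up to about one day then rests on self-report. This permits a small downward bias in the absolute 7-day proportion in both arms.

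The plausible size is about 0.1% to 1.6% in relative terms, assuming evenly spread contacts and no self-report. The figure of 12.5% to 14.3% needs every contact on Day 6, uniform onset and no self-report; it is a bound and not an expectation. The share actually contacted on Day 6 is unknown, and actual contact dates would settle it.

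The primary endpoint, the sample size and the efficacy analysis are not affected, and no bias between arms is indicated. Severity is low.

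**What to change.** 1. State which days form the 7-day period.
2. Set the Visit 2 window so that the AEFI contact cannot precede the end of that period, for example +7/-0 (Day 7 to Day 14), and restrict the AEFI form to events with onset in the period. This example fits a count of Days 0 to 6 or of seven elapsed days. If all of Day 7 is included, the window has to start on Day 8, or a partial-day gap remains.
3. For any contact made earlier, flag a no-event report as incomplete 7-day follow-up. This needs only the contact dates, so it can be applied even if visits have begun.

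The cost is one cell of Table 1, one definition and one data flag. No contacts are added. With +7/-0 the window shortens from 9 permitted days to 8, which leaves field staff slightly less room in scheduling.
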